6.6 Evaluation of Possible Guillain-Barré Syndrome

Subjects who develop any of the following symptoms will be requested to return to clinic within 24 hours for an unscheduled study visit to assess for Guillain-Barré Syndrome (‘Unscheduled visit’ in Appendices IA and IB):

- new onset of weakness of legs,
- tingling of hands and/or feet,
- difficulty walking

6.7 Management of Pregnancy on Study

HIV-1 infected women who are pregnant should be treated according to the Public Health Service Task Force Recommendations for Use of Antiretroviral Drugs in Pregnant HIV-

Infected Women for Maternal Health and Interventions to Reduce Perinatal HIV  
Transmission in the United States: Tables - April 29, 2009  
(<http://www.aidsinfo.nih.gov/Guidelines/> )

NOTE: The protocol team encourages the clinical sites to prospectively register the subject's pregnancy in the Antiretroviral Pregnancy Registry.  
(<http://www.apregistry.com/reg.htm> (In US: [name])).

6.71 Women who become pregnant after receipt of Dose #1 but before Dose #2  
Women who have received Dose #1 and are found to be pregnant prior to the Dose #2, will have entry into STEP II delayed until  $\geq 14$  weeks of gestation and with permission of their obstetrician. These women will also have an additional clinic visit within 28 days post delivery, as will their infant. Given the increased morbidity and mortality of pandemic H1N1 influenza in pregnant women, completion of the vaccine series is important to their health and, potentially, the health of their infant. These women will be followed as described in Appendix IB.

6.72 Women who become pregnant after Dose #2.  
Women who become pregnant after Dose #2 will remain on study with study evaluations as described in Appendix IA.

6.73 Termination of Pregnancy  
If a pregnancy is terminated, either spontaneously or electively, the site must notify the P1088 team for instructions ([[contact]](mailto:[contact]) )

## 6.8 Permanent Study Discontinuation

Criteria for discontinuation from the study are as follows:

- Loss to follow up.
- Subject withdrawal of consent.
- The investigator determines that further participation would be detrimental to the subject's health or well-being.
- The subject fails to comply with the study requirements so as to cause them self harm.

This study may be terminated for safety concerns of the PI, FDA, OHRP, DAIDS, DMID, SMC, participating Institutional Review Boards or Ethics Committees, and other governmental agencies.

## 7.0 EXPEDITED ADVERSE EVENT REPORTING

### 7.1 Expedited Adverse Event Reporting to DAIDS

The adverse events (AEs) that must be reported in an expedited fashion to DAIDS Regulatory Compliance Center (RCC) Safety Office include all serious adverse events (SAEs) as defined by ICH guidelines regardless of relationship to the study agent(s). A Serious Adverse Event (SAE) is any untoward medical occurrence that at any dose:

- Results in death
- Is life-threatening
- Requires inpatient hospitalization or prolongation of existing hospitalization
- Results in persistent or significant disability/incapacity, or
- Is a congenital anomaly/birth defect

Important medical events that may not be immediately life-threatening or result in death or hospitalization but may jeopardize the patient or may require intervention to prevent one of the outcomes listed in the definition above must also be reported in an expedited timeframe to DAIDS. Such determination may be made through medical or scientific judgment [ICH E2A]

In addition to reporting all SAEs as defined above, other events that sites must report in an expedited fashion include:

- Symptoms of Guillain-Barre Syndrome such as tingling of hands and/or feet, weakness of legs and new onset of difficulty walking

For all SAE's submitted to RCC, sites must file an updated SAE report to RCC with the final or stable outcome (Status Code p. 5 of the EAE form) unless the SAE reported in the initial EAE form already had a final or stable outcome.

---

 The term "life-threatening" refers to an event in which the patient was at risk of death at the time of the event.

 Per ICH SAE definition, hospitalization itself is not an adverse event, but is an outcome of the event. Thus, hospitalization in the absence of an adverse event is not regarded as an AE, and is not subject to expedited reporting.

The following types of hospitalization do not require expedited reporting to DAIDS:

- Any admission unrelated to an AE (e.g. for labor/delivery, aging-related cosmetic surgery, administrative admission, or social admission for temporary placement for lack of place to sleep)
- Protocol-specified admission (e.g. for procedure required by protocol)
- Admission for diagnosis or therapy of a condition that existed before receipt of study agent(s) (unless it is a worsening or increasing in frequency as judged by the clinical investigator)

Note: A new AIDS-defining event in a subject already known to be HIV-infected would be considered a worsening of a pre-existing condition (HIV infection).

The study agents for which relationship assessments are required are **Novartis Influenza A (H1N1) 2009 monovalent vaccine**.

The Division of AIDS Table for Grading the Severity of Adult and Pediatric Adverse Events, Version 1.0, dated December 2004, **Clarification August 2009**, must be used and is available on the RCC web site (<http://rcc.tech-res.com/safetyandpharmacovigilance/>).

The protocol-defined expedited event reporting period for this protocol is the entire study duration for an individual subject (from study enrollment until study completion or discontinuation of the subject from study participation for any reason).

After the end of the protocol-defined reporting period defined above, sites must report clinical events that are serious, unexpected adverse drug reactions if the study site staff becomes aware of the event on a passive basis, i.e., from publicly available information.

The timelines and mechanisms for reporting all the events listed above to the DAIDS Regulatory Compliance Center (RCC) Safety Office are defined in the “Manual for Expedited Reporting of Adverse Events to DAIDS” (DAIDS EAE Manual), dated May 6, 2004. The DAIDS EAE Manual is available on the RCC website: <http://rcc.tech-res.com/safetyandpharmacovigilance/>.

Sites using the DAERS internet-based reporting system for submission of EAEs to DAIDS will follow DAERS processes as outlined in DAERS training information. For questions about DAERS, please contact DAIDS-ES at [[contact]](mailto:[contact]) or from within DAERS application itself.

If the site cannot use DAERS to report an AE on an expedited basis, the AE must be documented on the DAIDS Expedited Adverse Event Reporting Form (EAE Reporting Form) available on the RCC website: <http://rcc.tech-res.com/safetyandpharmacovigilance/> and submitted as specified by the DAIDS EAE Manual. For questions about EAE reporting, please continue to contact the RCC.

## 8.0 STATISTICAL CONSIDERATIONS

### 8.1 General Design Issues

This is a Phase II study in children and youth  $\geq 4$  years to  $< 25$  years old who were infected with HIV-1 via perinatal transmission. This study is designed to investigate the safety, reactogenicity, and immunogenicity of a two dose regimen of Novartis **Influenza A (H1N1) 2009 monovalent vaccine**.

The sample will be stratified into 3 age strata, which may differ with respect to immune response. Moreover, factors such as immune status at the time of first immunization and differences in background exposure to the virus across sites participating in the study

may have an impact on response to the vaccine. The study will not have an adequate sample size to provide precise estimates of immune response and adverse events rates for all subgroups which may exhibit differing results. Section 8.6 presents confidence intervals around potential subgroups of various sizes with a range of potential results to provide an indication of the precision with which these rates can be estimated.

The study will be monitored intensely by the protocol team, which will review data every other week while subjects are accruing and the vaccine is being administered and at least once a month after the last dose of study vaccine has been administered (See Section 8.5). A Safety Monitoring Committee (SMC) will be convened by IMPAACT to review safety information gathered from all study participants.

## 8.2 Endpoints and Outcome Measures

### 8.21 Primary Endpoints:

#### 8.211 Adverse Events of Grade 3 or higher severity, including:

- Abnormal laboratory values, signs and symptoms or diagnoses.
- Solicited local AEs, including pain, tenderness, redness, and swelling post each vaccination.
- Solicited systemic AEs, including feverishness, malaise, body aches (exclusive of the injection site), nausea, and headache post each vaccination.

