4.3 Inclusion Criteria for STEP II

- 4.31 Received the first dose of **Influenza A (H1N1) 2009 monovalent study vaccine** at least 21 days ago.
- 4.32 Has a documented platelet count of  $>50,000$  per  $\text{mm}^3$  and an ANC of  $>500$  per  $\text{mm}^3$  within the 30 days prior to Step II entry.
- 4.33 Females of child-bearing potential must have a negative pregnancy test within 72 hours of Step II entry.

OR

If a woman became pregnant after Dose #1, she must be  $\geq 14$  weeks of gestation and have her obstetrician's permission to receive the vaccine.

NOTE: For management of women, who become pregnant after Dose #1, see section 6.7.

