## 8.6 Analyses

### 8.61 Primary Analyses

#### 8.611 Safety

The proportion of all subjects and of subjects within age strata experiencing grade 3 or grade 4 adverse events following the first and second doses of study vaccine will be presented. The precision with which these sample results estimate the rate of similar adverse events in the population represented by the study sample will be reported in terms of 90% confidence intervals (CI) around the sample proportions. This will provide 95% confidence that the rate of severe adverse effects is not greater than the upper limit of the CI around the proportion of subjects with grade 3+ events in the study sample.

Table 1 illustrates the confidence intervals for a range of hypothetical proportions of adverse events. This table shows (e.g.) that a sample finding of no grade 3+ adverse events in a total evaluable sample of 120 subjects would provide 95% confidence that the rate in the population from which the sample was drawn is no greater than 2%. A similar finding within a subsample of 20 subjects would provide 95% confidence that the population rate was no greater than 14%.

Table 1: Exact 90% Confidence Intervals around Potential Proportions of Subjects Exhibiting Grade 3+ Adverse Events (Total Sample and Selected Subsample Sizes)

| N   | Samples Rate | Lower Limit | Upper Limit |
|-----|--------------|-------------|-------------|
| 120 | 0%           | 0%          | 2%          |
|     | 5%           | 2%          | 10%         |
|     | 10%          | 6%          | 16%         |
|     | 25%          | 19%         | 32%         |
|     | 50%          | 42%         | 58%         |
| 40  | 0%           | 0%          | 7%          |
|     | 5%           | 1%          | 15%         |
|     | 10%          | 3%          | 21%         |
|     | 25%          | 14%         | 39%         |
|     | 50%          | 36%         | 64%         |
| 20  | 0%           | 0%          | 14%         |
|     | 5%           | 0%          | 22%         |
|     | 10%          | 2%          | 28%         |
|     | 25%          | 10%         | 46%         |
|     | 50%          | 30%         | 70%         |

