7. Reactogenicity assessments will briefly review the subject's history and provide an assessment of AEs at 30 minutes post vaccination and at all telephone calls. Assessments will include review of:
  - erythema,
  - induration,
  - pain and tenderness at the injection site,
  - fever,
  - fatigue,
  - myalgia (exclusive of the injection site),The following clinical evaluations will also be collected by interviewing the subject:
  - Assessment of eligibility prior to Dose #1 and Dose #2
  - All unplanned health care provider visits will be reported on the appropriate CRF.
8. Chemistries (SGOT, SGPT and creatinine ONLY) should be obtained within 30 days prior to administration of Dose #1 to obtain a baseline record. The same chemistries should be repeated at the STEP II Day 10 visit, to determine any liver or renal toxicity related to study vaccine.
9. CBC within 30 days; chart abstraction may be used
10. Immunophenotyping, including CD4, CD8, and CD19, within 30 days prior to study entry. Testing obtained for clinical care may be used if available. If not available, study specific immunophenotyping should be obtained. It may be run in the CLIA certified laboratory, at the clinical site. It does not need to be run at a DAIDS IQA certified laboratory.

11. HIV-1 RNA obtained from medical record within 30 days of study entry. It may be run in the CLIA certified laboratory, at the clinical site. It does not need to be run at a DAIDS VQA certified laboratory.
12. Blood draw volumes for PBMC/plasma for the various age groups should be no more than the following:  
     $\geq 4$  to  $< 6$  years of age: 11.0ml  
     $\geq 6$  to  $< 25$  years of age: 20.0ml
13. Directions for collection, processing, storage and shipping can be found in the P1088 Manual of Operations (MOP) and the Laboratory Processing Chart (LPC).
14. HAI will be performed for **H1N1 2009 H1N1 Influenza A virus** at all visits and for influenza viruses contained in the 2009-2010 vaccine preparation at the screening and 7 month visits.

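### Primary endpoint 8.211 counts headache and nausea as solicited but neither reactogenicity checklist names them, and Appendix IA schedules no laboratory panel after both doses

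*Combined protocol and SAP*

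**What the plan says.** **Endpoint.** Section 8.211 defines the first primary safety endpoint as adverse events of Grade 3 or higher. Its components include "Abnormal laboratory values, signs and symptoms or diagnoses" and, in a separate bullet, "Solicited systemic AEs, including feverishness, malaise, body aches (exclusive of the injection site), nausea, and headache post each vaccination".

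**Analysis.** Section 8.611 says that the proportion of subjects "experiencing grade 3 or grade 4 adverse events following the first and second doses of study vaccine will be presented", overall and by age stratum, with 90% confidence intervals.

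**Symptom collection.** Appendix IA footnote 7 states: "Reactogenicity assessments will briefly review the subject's history and provide an assessment of AEs at 30 minutes post vaccination and at all telephone calls". It then lists erythema, induration, injection-site pain and tenderness, fever, fatigue and, last, "myalgia (exclusive of the injection site"). Appendix IB footnote 6 gives the same list.

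**Laboratory collection.** In Appendix IA, chemistries appear at Screen and Step II Day 10. Footnote 8 says: "The same chemistries should be repeated at the STEP II Day 10 visit". The CBC appears at Screen and Step I Day 21, under footnote 9: "CBC within 30 days; chart abstraction may be used". Criterion 4.32 accepts platelet and neutrophil counts documented "within the 30 days prior to Step II entry".

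**The concern.** A term called solicited in a primary endpoint should be one that every subject is asked about, in the same way, at the same contacts. If some systemic terms are prompted and others are left to a general question, their rates are not comparable. Those left to the general question are likely to be under-counted. The two missing terms are not marginal: section 9.31 names both headache and nausea among the expected reactions and says that such reactions may be more frequent at the higher dose level, which is the one this trial gives.

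The laboratory part of the endpoint raises a different problem. A by-dose table of Grade 3 or 4 events invites the reader to compare doses. If a panel is not scheduled after one of the doses, a zero for that dose may mean only that nobody was tested.

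**Working it through.** **1. Terms side by side**

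| Term in 8.211 | Checklist (IA footnote 7, IB footnote 6) |
|---|---|
| pain, tenderness | pain and tenderness |
| redness | erythema |
| swelling | induration (approximate) |
| feverishness | fever |
| body aches | myalgia |
| malaise | fatigue (approximate) |
| nausea | not named |
| headache | not named |

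Of the five solicited systemic terms, two have no checklist item and a third has only an approximate one.

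**2. Laboratory tests by dose (Appendix IA)**

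| Panel | Before Dose #1 | After Dose #1, before Dose #2 | After Dose #2 |
|---|---|---|---|
| Chemistries | Screen | none | Step II Day 10 |
| CBC | Screen | Step I Day 21 | none |

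The blood-volume totals confirm this reading:
- Day 21: 1 (CBC) + 11 to 20 (PBMC) + 2 (HAI) = 14 to 23 ml, as stated, leaving no room for chemistries.
- Step II Day 10: 2 (chemistries) + 11 to 20 + 2 = 15 to 24 ml, as stated, leaving no room for a CBC.

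Appendix IB differs. Women who become pregnant between doses have chemistries before Dose #2 and again 10 days after it.

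**3. Reach of the CBC look-back**

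Inputs: a 30-day window (footnote 9; criterion 4.32) and Dose #2 at 21 to 28 days after Dose #1. Reach before Dose #1 = 30 − interval.
- Dose #2 on Day 21: 30 − 21 = 9 days before Dose #1.
- Dose #2 on Day 28: 30 − 28 = 2 days before Dose #1.

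A baseline CBC drawn on Day 0 before vaccination is 21 to 28 days old at Step II entry, so it is always inside the window. Appendix IA footnote 1 prefers screening and entry on the same day, so such a value will often exist.

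**4. The plan's precision figures, and what they assume**

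With 0 of n events, the upper 90% limit is 1 − 0.05^(1/n).
- n = 120: 2.47% (plan: 2%).
- n = 20: 13.91% (plan: 14%).

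For Table 2 with N = 120:
- P(at least 1) at a 2% rate = 1 − 0.98^120 = 91.1% (plan: 91%).
- P(at least 2) at a 3% rate = 1 − 0.97^120 − 120 × 0.03 × 0.97^119 = 87.8% (plan: 88%).

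The plan's figures are correct, but they take every event as ascertained. As illustration only, let s be the share of true events that is ascertained. The documents give no value for s. Divide the upper limit by s, and replace p by p × s in the probabilities:

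| s (assumed) | Upper limit on true rate, 0 of 120 | P(at least 1), true 2% | P(at least 2), true 3% |
|---|---|---|---|
| 1 | 2.5% | 91% | 88% |
| 0.9 | 2.7% | 89% | 84% |
| 0.75 | 3.3% | 84% | 75% |
| 0.5 | 4.9% | 70% | 54% |

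For an analyte not drawn after a given dose, s for that dose is close to 0 unless the test is done for clinical care.

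**The case against.** The strongest reply is that nothing is lost from the endpoint.
- Section 8.211 counts Grade 3 or higher signs and symptoms generally, so a severe headache counts whether or not it was prompted.
- Section 6.1 requires adverse events of all grades on the CRF. Appendix IA footnote 6 has staff ask about adverse events at each contact, and section 6.2 asks subjects to return for Grade 3 or 4 events possibly associated with vaccine.
- The checklist may not be exhaustive, and severe symptoms are more likely to be volunteered than mild ones.
- The memory aid and CRF are not in the documents and may already list the missing terms.

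This stands. A reader might infer that headache and nausea go uncaptured, or that the primary rate and the halting rule on subjective reactions are biased low by a known amount. The documents support neither. The gap is between prompted and general inquiry, and its size is unknown.

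On laboratory events, a reader might infer that none is measured after each dose, or that post-Dose-1 chemistry is missing for everyone. That is also too strong. A CBC follows Dose #1, chemistries follow Dose #2, and Appendix IB schedules chemistries before Dose #2. The laboratory bullet of 8.211 does not itself require measurement after each vaccination; the by-dose presentation comes from 8.611, which does not single out laboratory events. The Day 21 volume total includes a fresh CBC, so the chart value is a permitted alternative rather than the planned path.

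What the reply does not remove is the solicited label on unprompted terms, the lack of any Appendix IA panel after both doses, and a look-back that admits a pre-vaccination count.

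**Conclusion.** The point holds as a mismatch between the primary endpoint and the schedule that feeds it. Two of five solicited systemic terms are on neither checklist and a third is matched only approximately, so under-ascertainment relative to the prompted terms is likely but cannot be quantified from the documents. Under Appendix IA no laboratory panel is scheduled after both doses. The CBC meant to follow Dose #1 can be a value from up to 2 to 9 days before it. A by-dose table could therefore show no events where there was no test.

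This rests on reading the footnote lists as the solicitation instrument, and on counting the 30 days of footnote 9 back from Step II entry, as 4.32 does. If the memory aid and CRF already prompt for headache, nausea and malaise, the symptom part reduces to correcting two footnotes. The laboratory part would remain.

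**What to change.** 1. Add headache, nausea and malaise to Appendix IA footnote 7 and Appendix IB footnote 6, and confirm that the memory aid and reactogenicity CRF match 8.211. If any subjects were assessed under the present list, note in the safety tables that these terms were not prompted for them.
2. State in footnote 9 that the CBC used for post-Dose-1 safety reporting must be drawn after Dose #1. This concerns reporting only and leaves criterion 4.32 as it is.
3. State in 8.611 that laboratory events are reported cumulatively, or only for the dose after which that panel was scheduled, with the number of subjects tested as denominator.

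The cost is a few more questions at contacts already planned, some wording, and possibly slightly higher reported event rates. If the team wants true by-dose laboratory rates, 2 ml for chemistries at Day 21 and 1 ml for a CBC at Step II Day 10 would supply them at visits that already draw blood. That is optional; item 3 suffices without it.

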#### 8.212 Adverse Events of Grade 3 or higher severity attributed to the study vaccine.

#### 8.213 Second vaccine dose withheld, due to adverse reactions attributed to first dose.

#### 8.214 Immunologic response, defined as HAI titer $\geq 1:40$ , at 21 days after Dose #1 and at 10 days after Dose #2.

